## Protocol ID NL42367.018.12

## Reflux symptoms in achalasia

compared to patients without GER symptoms. A higher mean LES pressure could contribute to retention and fermentation of food in the esophagus. In general, treated patients with a mean LES pressure  $\leq 10$  mmHg are in remission. Therefore we expect that the LES pressure in patients without GER symptoms is  $\leq 10$  mmHg and in patients with GER symptoms  $> 10$  mmHg. We consider a difference of 5 mmHg in LES pressure as clinically relevant. When, using a two-group t-test with a two-sided significance level of 5% and a power of 80%, the sample size required in each group is 18 study subjects. For this calculation we assumed that the LES pressure in patients without GER symptoms is 10 mmHg or lower and for patients with GER symptoms we assumed a LES pressure of 15 mmHg or higher. The common standard deviation was assessed at 5.1 mmHg for both groups.

Previous studies did not investigate the role of esophagogastric junction distensibility and esophageal stasis in treated achalasia patients with GER symptoms. Therefore for these parameters, we estimated the difference between the two groups that in our opinion could be clinically relevant. Our hypothesis is that GER symptoms are dependent on retention and fermentation of food due to a reduced clearance by aperistalsis of the esophageal body. Consequently, we expect that the esophagogastric junction (EGJ) distensibility in the group with GER symptoms is decreased and esophageal stasis is increased.

The cut-off for normality of the EGJ distensibility in healthy controls is 2.9 mm^2/mmHg. Values below this cut-off point are considered as a decreased EGJ distensibility. Therefore we expect that in the group without GER symptoms the EGJ distensibility is  $\geq 2.9$  mm^2/mmHg and in the group with GER symptoms the EGJ distensibility is  $< 2.9$  mm^2/mmHg. A sample size of 12 study subjects in each group will have 80% power to detect a difference in means of at least 1.2 mm^2/mmHg using a two group t-test with a 0.05 two-sided significance level. In this calculation we assumed that patients without GER symptoms have a mean EGJ distensibility of 4.0 mm^2/mmHg and a mean EGJ distensibility of 2.8 mm^2/mmHg or lower is considered as a significant decreased distensibility of the EGJ which is expected in the group with GER symptoms. The common standard deviation was assessed at 1.0 mm^2/mmHg for both groups.

When a barium esophagogram is performed in healthy volunteers there is no stasis of contrast in the esophagus. In achalasia patients, generally there is stasis of contrast during a barium esophagogram, in both treated as untreated patients. Stasis of contrast  $\geq 5$  cm is considered as significant in treated achalasia patients. We expect that in patients with GER symptoms esophageal stasis is increased,  $\geq 5$ cm, compared to patients without GER symptoms. In general all achalasia patients will have some esophageal stasis even without

**Protocol ID NL42367.018.12****Reflux symptoms in achalasia**

complaints. Studies have shown that treated patients in remission still have some esophageal stasis, approximately 3.8 cm on the barium esophagogram (rohof). Based on these data we assessed the sample size. A sample size of 17 study subjects in each group will have 80% power to detect a difference in means of at least 1.2 cm using a two group t-test with a 0.05 two-sided significance level. This calculation is based on the assumption that patients without GER symptoms have on the barium esophagogram stasis of around 3.8 cm and stasis of 5 cm or higher is considered as a significant stasis which is expected in patients with GER symptoms. The common standard deviation was assessed at 1.2 cm for both groups.

In the Netherlands a large part of the patients with achalasia are referred to the Motility Centre of the AMC for diagnosis and treatment. Therefore we believe that the number of patients visiting our department is sufficiently high to find enough participants for the study.

**5. METHODS****5.1 Study parameters****5.1.1 Primary study parameter**

- Gastroesophageal reflux episodes

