## 2. OBJECTIVES

Our hypothesis is that gastroesophageal reflux symptoms in treated patients with achalasia are dependent on retention and fermentation of food due to a reduced clearance by aperistalsis of the esophageal body rather than the result of true acid reflux episodes. We expect a difference in gastroesophageal reflux episodes, LES pressure, sensitivity to acid and esophageal distension in the treated patients with achalasia that experience

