### 4.4 Sample size

Treated achalasia patients with or without gastroesophageal reflux symptoms will be included. Per group we aim to include 20 study subjects. In the literature the incidence of GER symptoms in patients with achalasia post-treatment is very variable. Articles describe an incidence that differs between 10% up till 60%. This variability in the incidence is probably caused by the different diagnostic approaches in these studies. Furthermore the GER symptoms do not always correlate with a positive pH-impedance monitoring for GERD or fermentation of food.

Based on this we expect that 30% of the patients without GER symptoms will have gastroesophageal reflux episodes caused by GER or fermentation of food. For the patients with GER symptoms we estimate that in 75% gastroesophageal reflux episodes occur caused by GER or fermentation. We consider a 45% difference in gastroesophageal reflux episodes between the two groups as clinically relevant. When, using a two-group chi-square test with a two-sided significance level of 5% and a power of 80%, the sample size required in each group is 19 subjects. Based on this we aim to include 40 study subjects. Below we have calculated the sample sizes based on our main secondary study parameters to show that with a sample size of 40 study subjects it is possible to attain these secondary study parameters.

We believe that the three main secondary study parameters are LES pressure, esophagogastric junction distensibility and the level of esophageal stasis. Several studies have described that true GERD occurs in patients with a lower mean LES pressure post-treatment. However, other studies contradict these findings. Based on our hypothesis we believe that patients with GER symptoms have a higher mean LES pressure post-treatment

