**Protocol ID NL42367.018.12****Reflux symptoms in achalasia**

pH 7 and pH 1. The catheter will be positioned in such a way that the pH sensor is located 5 cm above the LES, which is based on manometry readings.

*Analysis of the data of the HRM and pH-impedance monitoring*

For analysis of the data obtained with HRM and pH-impedance measurement MMS software (Enschede, The Netherlands) will be used. Observers will be blinded for patient characteristics when analyzing the measurement.

The HRM will give insight in the esophageal function. It provides information on the contractile activity of the esophageal body and the esophagogastric junction including the LES. Therefore it is helpful in distinguishing transient LES relaxation (TLESRs), which occurs in GERD, from pseudorelaxation of the LES by shortening of the esophageal body. pH-impedance monitoring provides information on esophageal bolus transit. Combined with HRM it can distinguish GER from retention and fermentation of food. GER is characterized by TLESRs and a retrograde moving decrease in impedance with an abrupt drop in pH levels followed by normalisation of the impedance and pH. In case of fermentation there is a slow and longer decrease in impedance and pH. The pH-impedance monitoring will also record all reflux episodes, both acid as non-acid, during the 24-hours measurement. During the analysis of the data of the pH-impedance monitoring reflux symptoms will be correlated with acid and non-acid reflux episodes. A positive correlation is declared if a specific reflux symptom is preceded by a reflux episode within two minutes.

*Acid perfusion test*

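### The primary endpoint, as powered, pools reflux with fermentation, so it cannot test the hypothesis that symptoms come from fermentation rather than true reflux

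*Protocol*

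**What the plan says.** Section 5.1.1 of the protocol gives the primary parameter as "Gastroesophageal reflux episodes" and nothing more. It does not say whether this is a yes/no status or a count, or whether fermentation belongs to it.

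Section 4.4 supplies the only numbers. For the group without symptoms, "we expect that 30% of the patients without GER symptoms will have gastroesophageal reflux episodes caused by GER or fermentation of food". The corresponding estimate in symptomatic patients is 75%, again for either cause. The planned test is a two-sided chi-square at 5% with 80% power, for which "the sample size required in each group is 19 subjects"; the aim is 20 per group. The target is worded as "We consider a 45% difference in gastroesophageal reflux episodes between the two groups as clinically relevant".

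Section 2 states the hypothesis: symptoms are held to be "dependent on retention and fermentation of food due to a reduced clearance by aperistalsis of the esophageal body rather than the result of true" reflux of acid. In section 5.2.2, the part on analysing the manometry and pH-impedance data says that the combined measurement can tell the two apart. Reflux is an abrupt pH fall that normalises, whereas "In case of fermentation there is a slow and longer decrease in impedance and pH". Section 1 likewise contrasts reflux episodes with periods of stasis.

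Section 8 uses chi-square for categorical variables and leaves numerical comparisons to the distribution of the data, so both a yes/no and a count analysis remain open.

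**The concern.** The hypothesis is about which of two mechanisms produces symptoms. The endpoint that carries the sample size scores a patient as positive for either. A difference between groups then says that something happens more often in symptomatic patients, but not which of the two. A null result is no clearer, because reflux that is common in both groups would make patients positive whatever their fermentation status and shrink a real fermentation difference.

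The information needed to avoid this is planned for collection, since section 5.2.2 describes how each event type is recognised. What is at stake is whether the primary result can answer the question in section 2.

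**Working it through.** **1. The plan's own figure.** Inputs from section 4.4: p1 = 0.30, p2 = 0.75, two-sided 5%, power 80%. The mean proportion is 0.525.

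n = [1.960 × √(2 × 0.525 × 0.475) + 0.842 × √(0.30 × 0.70 + 0.75 × 0.25)]² / 0.45² = (1.384 + 0.531)² / 0.2025 = 18.1, so 19 per group.

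The stated 19 is reproduced (chi-square, no continuity correction). The powered endpoint is therefore one yes/no per patient. Exact power at 20 per group is 82%.

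**2. The pooled result does not identify the mechanism.** Let F be the proportion with fermentation and R the proportion with reflux, taken as independent. The pooled proportion is 1 − (1 − F)(1 − R). Three different states of nature give the same 30% v 75%:

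| State | F, without v with symptoms | R, without v with symptoms | Pooled |
|---|---|---|---|
| Fermentation only | 30% v 75% | 0% v 0% | 30% v 75% |
| Reflux only | 0% v 0% | 30% v 75% | 30% v 75% |
| Equal fermentation, reflux differs | 20% v 20% | 12.5% v 68.75% | 30% v 75% |

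Check of the third row: 1 − 0.80 × 0.875 = 0.30 and 1 − 0.80 × 0.3125 = 0.75. The first row supports the hypothesis and the other two contradict it. The primary test has the same 82% power in all three.

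**3. Masking on the yes/no scale.** Assume fermentation in 30% v 75% and the same reflux prevalence R in both groups. The documents give no value for R, so a range is shown. Power is by exact enumeration of the chi-square test at 20 per group.

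| R (assumed) | Pooled, without v with symptoms | Difference | Power |
|---|---|---|---|
| 0% | 30% v 75% | 45 points | 82% |
| 20% | 44% v 80% | 36 points | 67% |
| 50% | 65% v 87.5% | 22.5 points | 40% |
| 80% | 86% v 95% | 9 points | 13% |

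**4. If episodes are counted instead.** The documents give no counts or durations. As an assumed example, take 40 reflux episodes of 1 minute and 2 fermentation periods of 60 minutes. Fermentation is 2/42 = 4.8% of the count but 120/160 = 75% of the time.

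A simulation compared analyses at 20 per group. It assumed equal reflux in both groups (negative binomial, mean 5 to 30 per day, dispersion 1.5 to 3) and fermentation in 30% v 75% of patients (1 or 2 periods of 60 to 120 minutes). The tests rejected as follows:

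- Rank test on pooled counts: below or about 10% of trials, close to chance; roughly 35 to 39% if reflux is sparse (mean 1 per day).
- Rank test on fermentation time: about 75%.
- Chi-square on fermentation yes/no: about 82%.

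Most of the gain comes from separating fermentation from reflux. Measuring its duration adds no power in this scenario.

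**5. What separation does to the planned power.** The 30% and 75% were given for both mechanisms together, so fermentation rates may differ. Exact power at 20 per group under assumed splits:

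- Fermentation is half of each rate, 15% v 37.5%: 38%.
- Fermentation is two thirds of each rate, 20% v 50%: 53%.
- All events are fermentation, 30% v 75%: 82%.
- Reflux is 20% in both groups and the pooled rates stay at 30% v 75%, so fermentation is 12.5% v 68.75%: 98%.

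**The case against.** The strongest reply is that the power loss in step 3 rests on prevalences the plan does not expect. Section 4.4 puts reflux and fermentation together at 30% in patients without symptoms, so reflux in 50% or 80% of them contradicts the planning figure. If 30% and 75% are right as pooled rates, the pooled test keeps its 82%. This stands, and it makes the masking conditional. It does not remove the risk: section 5.2.2 records all acid and non-acid episodes over 24 hours and section 4.4 gives no threshold for a positive patient, so prevalence could be well above 30% if any episode counts. Nor does it touch step 2, which takes the pooled rates exactly as planned.

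A second reply is that esophageal stasis is a main secondary parameter with its own calculation of 17 per group. That is partial cover only. It is a barium column height at 1, 2 and 5 minutes, not fermentation over the 24-hour recording.

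A reader might infer something stronger: that an endpoint in episodes ignores duration and so gives fermentation, the longer event, almost no weight against many short reflux episodes. The protocol does not support this as a general statement. It fixes no count, and on the yes/no scale that yields the 19, one fermentation event makes a patient positive just as one or 40 reflux episodes would. The low weight arises only if a pooled count is analysed.

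**Conclusion.** The concern holds as a pooling defect. With the planned rates taken at face value, the primary comparison cannot distinguish the hypothesised mechanism from its rival, and this needs no assumed figures beyond the algebra in step 2. The loss of power from 82% to 67%, 40% or 13% is conditional: it assumes that 30% v 75% are fermentation rates, that reflux is equally common in both groups, that the two occur independently, and that any reflux makes a patient positive.

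It does not follow that time should replace the yes/no as the primary measure. A rank test on fermentation time has about 75% power against about 82% for fermentation yes/no in the scenario of step 4, whose counts and durations are all assumed. The absent duration measure is a smaller gap, worth filling with a secondary measure because section 5.2.2 itself describes fermentation as the longer event.

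**What to change.** - In sections 5.1.1 and 4.4, define the primary endpoint as fermentation present or absent per patient over the recording, compared by chi-square. State the rule that makes a patient positive.
- In section 4.4, either say that 30% and 75% apply to fermentation, in which case 19 per group stands, or give the expected fermentation rates and restate the power.
- Analyse true reflux separately, as a secondary comparison, so that there is still a single primary test.
- Add the percentage of recording time in fermentation and in reflux as secondary descriptive measures, with episode counts as description.

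The cost is protocol wording and one revised power statement. The recording is the same and no procedure is added for patients. Manometry covers only the first hours of the recording (half an hour fasting and 3.5 hours after the meal), so the rule must also say how events are classified in the remaining 20 hours from pH and impedance alone. The real downside is that the pooled rates may not carry over: under the splits in step 5, power at 20 per group runs from 38% to 98%, so the sponsor may find the study smaller than it needs to be for this question.

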**5.1.2 Secondary study parameter**

- LES pressure
- Esophagogastric junction distensibility
- Sensitivity to acid perfusion and distensibility
- Level of esophageal stasis
- Width/diameter of the esophagus

**5.2 Study procedures**

Treated patients with idiopathic achalasia visiting the outpatient clinic will be asked to participate in the study. Only when a study subject has given informed consent, questionnaires concerning demographic and clinical data will be recorded and measurements will be performed.

**5.2.1 Research protocol**

**Protocol ID NL42367.018.12****Reflux symptoms in achalasia**

Baseline clinical data will be collected using different questionnaires. Before any measurement will be performed the participant will be subjected to the GERD Questionnaire to be certain that he or she is allocated in the correct study group.

For this study all included study subjects will undergo five different measurements in two following days, as outlined in the schematic overview. The first measurement will be performed with impedance planimetry, using the Endo Functional Luminal Imaging Probe (EndoFLIP). The Endoflip can determine the esophagogastric junction distensibility and examine the esophageal distensibility. The measurement with the Endoflip will be followed by an acid perfusion test, the Bernstein test. The perfused catheter used for the high-resolution manometry will be used to infuse the acid and control solutions. The acid perfusion test will provide information about the sensitivity for acid in the esophagus. After the acid perfusion test a combined measurement of high-resolution manometry (HRM) and pH-impedance monitoring will be carried out. The catheter used for the acid perfusion test is the same as the catheter for the HRM. After 3-4 hours the HRM catheter will be removed and the pH-impedance catheter will remain in place for a further 24-hour measurement of reflux episodes and symptoms. After 24-hour pH-impedance monitoring the catheter will be removed and a timed barium esophagography will be performed. The barium esophagography is performed to gain insight into esophageal emptying and the width of the esophagus.

**Schematic view of the study design**[figure not shown]

**Protocol ID NL42367.018.12****Reflux symptoms in achalasia***Study requirements and timeline*

The measurements will be performed after cessation of PPIs, H2-antagonists and medications which can influence intestinal motility for 1 week. A temporary stop of PPI, H2-antagonist or prokinetic drug prior to reflux monitoring is not harmful for the patient and is in concordance with the reflux guideline of the Dutch association of gastroenterologists. For the reduction of severe symptoms patients are allowed to take rescue medication in the form of antacids. Furthermore, one day before the measurements the patients will be restricted to a liquid diet to minimise stasis of food in the esophagus.

Study subjects will arrive in the morning at the clinic after an overnight fast, no intake of fluid after midnight except water. Preferably the intake of medication should be postponed after the measurements. If this is not possible medication should of course be ingested prior to the measurements. Before the first measurements patients must have been fasting for two hours, so also no intake of water. The catheter for the Endoflip will be placed transnasally. After this measurement the catheters for the esophageal HRM and pH-impedance will be placed transnasally. Before placement of the pH-impedance catheter, an acid perfusion test will be performed using the HRM catheter. The combined HRM and pH-impedance measurement will be performed in the fasting condition for half an hour followed by a postprandial measurement of 3.5 hours after a standardized liquid meal, 400 mL nutrient drink (600 kcal Nutridrink, Nutricia, the Netherlands) with 200 mL water. The liquid meal will be administered by the catheter used for the HRM. After this the HRM catheter will be removed while the pH-impedance catheter will stay in place and reflux will be monitored for the next 20 hours. The standard investigation for patients with reflux symptoms is 24-hour pH-impedance monitoring. Study subjects go home with the pH-impedance catheter in place and will receive a diary to write down there symptoms. During this measurement the study subject has to drink and eat at regular moments but there is no restriction concerning the food intake, except again an overnight fast due the timed barium esophagography the next day. The following day patients come back to the clinic where the pH-impedance catheter will be removed and a timed barium esophagography will be performed, which is the last measurement.

**5.2.2 Procedures and questionnaires***Endo Functional Luminal Imaging Probe (EndoFLIP)*

To determine the distensibility of the esophagogastric junction (EGJ) and the esophagus the EndoFLIP system will be used (MMS, Enschede, the Netherlands). The measurement with the EndoFLIP will be performed according to a previously described protocol. A probe is

**Protocol ID NL42367.018.12****Reflux symptoms in achalasia**

inserted into the esophagus and placed at the level of the EGJ. The probe consists of a 240-cm catheter with a 14-cm bag attached to its distal end, which is compliant to a maximal diameter of 25 mm. Inside the bag 17 electrodes are placed at 4-mm intervals. An excitation current of 100µA is generated between two adjacent electrodes at a frequency of 5 kHz. Using impedance-planimetry cross sectional areas (CSAs) are determined for the 16 balloon cross sections during volume controlled distensions. Additionally two pressure sensors are located on the probe to determine intrabag pressure allowing assessment of EGJ distensibility.

The distension probe and the pressure transducers are calibrated by the manufacturer. The pressure sensor is zeroed prior to transnasally insertion of the catheter. Previous manometry readings of the study subjects will be used to position the balloon at the EGJ. The balloon will be inflated to a 20, 30, 40, 50, 60 and 70 mL volume. Pressures and CSAs are collected at a rate of 10 Hz. Distensibility is assessed using the median value over a 30 s dynamic measurement of the narrowest CSA, which corresponds to the EGJ, and the median intrabag pressure.

After measuring the EGJ distensibility the catheter will be placed 10 cm above the LES and the balloon will be inflated to a 20, 30, 40, 50, 60 and 70 mL volume. The time between each inflation will be 30 seconds and study subjects will be asked after each inflation whether they experience pain or other symptoms.

*High Resolution Manometry (HRM)*

A water-perfused high-resolution manometry assembly with 21 water-perfused sensors spaced at 1-cm intervals at the position of the esophagogastric junction will be used (Medical Measurement Systems, Enschede, The Netherlands). Each sensor is accurate to within 1 mmHg, capable of recording transient pressure changes in excess of 6000 mmHg/s, and zeroed to atmospheric pressure. The high-resolution manometry assembly will be introduced transnasally and positioned to record from hypopharynx to stomach with about five intragastric sensors. Data are analyzed using Solar high-resolution manometry software (Medical Measurement Systems, Enschede, The Netherlands).

*pH- impedance monitoring*

A pH-impedance catheter will be introduced transnasally. A 2.1-mm outer diameter study catheter comprised of six electrode pairs measuring intraluminal impedance at 3, 5, 7, 9, 15 and 17 cm above the LES and an ISFET pH sensor, placed 5 cm above the LES will be used. Before and after recording the pH electrode will be calibrated using standard buffers of

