**Main study parameters/endpoints:**

*Primary:*

- Gastroesophageal reflux episodes

*Secondary:*

- LES pressure
- Esophagogastric junction distensibility
- Sensitivity to acid perfusion and distension
- Level of esophageal stasis
- Width/diameter of the esophagus.

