**6.2 Adverse events and serious adverse events**

All the measurements that are performed are safe procedures and routinely performed in the clinical setting, with rarely any serious complications. Possible complications are mainly due to placement of the catheters. The catheters can give discomfort in the nose and pharynx. Furthermore in rare cases a mucosal bleeding of the nose, caused by the catheter, can occur which never need extra treatment. All adverse events reported spontaneously by the subject or observed by the investigators will be recorded in a database.

All serious adverse events (SAEs) will be reported through the web portal *ToetsingOnline* to the accredited METC that approved the protocol. The SAEs will be reported within 15 days after the sponsor is first notified of the SAEs.

The SAEs that result in death or are life treating will be reported expedited through the web portal *ToetsingOnline* to the accredited METC that approved the protocol. This will not occur later than 7 days after the coordinating investigators and principal investigator have knowledge of the SAE(s). This first report is preliminary and within 8 days after submission of the first report a final report will be submitted.

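### Sensitivity to distension is asked about only from 20 mL upward, so a symptom reported at 20 mL cannot be told apart from one already present before inflation

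*Protocol*

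**What the plan says.** The Summary lists "Sensitivity to acid perfusion and distension" among the secondary parameters. Section 5.1.2 words the same item as "Sensitivity to acid perfusion and distensibility", but the Objectives make the intended meaning clear: "We expect a difference in gastroesophageal reflux episodes, LES pressure, sensitivity to acid and esophageal distension" between the groups with and without reflux symptoms.

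The only description of how sensitivity to distension is measured is in 5.2.2, under EndoFLIP. The bag is first inflated through six volumes at the esophagogastric junction (EGJ) to obtain distensibility. Then "the catheter will be placed 10 cm above the LES and the balloon will be inflated to a 20, 30, 40, 50, 60 and 70" (all volumes in mL). Successive inflations are 30 seconds apart. On symptoms, the section says only this: "study subjects will be asked after each inflation whether they experience pain or other symptoms". The protocol describes no rating with the bag in position and empty, no sham inflation, no symptom scale, and no rule for a symptom that was there beforehand.

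Three other places bear on the point:
- **Groups (4.2.1, 4.2.2).** One group has a GERDQ score of at least 8 and symptoms for more than 3 months. The other scores below 8 and has no symptoms.
- **State at testing (5.2.1).** "The measurements will be performed after cessation of PPIs, H2-antagonists and medications which can influence intestinal motility for 1 week". This holds for all subjects, and antacids are permitted for severe symptoms.
- **Catheter effects (6.2).** "The catheters can give discomfort in the nose and pharynx".

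**The concern.** A sensitivity threshold is the lowest stimulus at which a new sensation appears, so the state before the stimulus has to be known. Here the first recorded state is at 20 mL. A patient who already has heartburn or chest pain can truthfully report a symptom at the first step and will look like a patient who reacts to the smallest distension.

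The two groups are defined by whether they have background symptoms, so such reports may be more frequent in one group even if sensitivity is the same in both. The comparison could then point to heightened sensitivity as a mechanism, which the Introduction names as a candidate explanation, when none exists. This concerns data collection: a state that was never recorded cannot be recovered by any later analysis plan.

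**Working it through.** **1. The two halves of the sensitivity parameter, side by side (5.2.2)**

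| Feature | Acid perfusion | Distension |
|---|---|---|
| Period before the stimulus | 10 min adaptation, then 10 min saline | none described |
| Subject blinded to the stimulus | yes | not stated |
| Sensations recorded | first perception, discomfort and pain, timed | pain or any other symptom |
| Change from the previous state asked | every minute | not stated |
| Immediately preceding step | EndoFLIP | six EGJ inflations up to 70 mL |

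The acid test has a reference phase and the distension test has none. The GERDQ completed before the measurements (5.2.1) confirms group allocation; it does not rate current symptoms with the catheter in place.

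**2. The plan's own figures**

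Section 4.4 gives no sample size for this parameter, so no stated figure is in question. The planned 20 per group comes from the primary calculation, 30% v 75%. With a mean proportion of 0.525:

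n = [1.960·√(2·0.525·0.475) + 0.842·√(0.30·0.70 + 0.75·0.25)]² / 0.45² = (1.384 + 0.531)² / 0.2025 ≈ 18.1, rounded up to 19, as stated.

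**3. Illustration of size**

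Assumptions, none of them in the protocol:
- Both groups have the same true sensitivity.
- A share b has a symptom before inflation.
- Every such symptom is counted as a response at 20 mL.

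*Share reporting at 20 mL* = b + (1 − b)·h, where h is the chance of a first true response at a step. With h = 10%:
- b = 5%: 0.05 + 0.95·0.10 = 14.5%
- b = 10%: 0.10 + 0.90·0.10 = 19%
- b = 20%: 0.20 + 0.80·0.10 = 28%
- b = 30%: 0.30 + 0.70·0.10 = 37%
- b = 50%: 0.50 + 0.50·0.10 = 55%

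*Analysis A*: Mann-Whitney test on the first-symptom volume, non-responders ranked last, 20 v 20, two-sided 5%, simulated.

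*Analysis B*: uncorrected chi-square test on any response, exact enumeration, 20 v 20. The observed share is p + (1 − p)·b, where p is the true response. For p = 30%, for example, b = 30% gives 0.30 + 0.70·0.30 = 51%, and b = 5% gives 0.30 + 0.70·0.05 = 33.5%.

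| Symptomatic before inflation, symptom v comparison group | A: false-positive rate | B: p = 30% / p = 50% |
|---|---|---|
| 0% v 0% | 4.6% (h = 10%) | 5.3% / 4.3% |
| 10% v 5% | 5–6% (h = 10–40%) | not run |
| 20% v 5% | 7–12% (h = 10–40%) | 10.2% / 6.9% |
| 30% v 5% | 14–30% (h = 5–40%) | 19.0% / 11.9% |
| 50% v 5% | 36–67% (h = 10–40%) | not run |
| 50% v 10% | not run | 40.2% / 26.9% |

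Equal background shares leave the rate at 4–5% (20% in each group under A, 10% in each under B). What matters is the gap between the groups, not the presence of background symptoms as such. In A, the larger h is, the smaller the inflation.

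**The case against.** Much can be said against a strong form of this point.

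- **Scoring.** A reader might infer that pre-existing symptoms are scored as sensitivity. The protocol states no scoring rule. It names pain separately from other symptoms, so an analysis could use pain alone, and section 8 leaves the numerical test open. What stands is that such symptoms cannot be separated and so can be counted.
- **Catheter and drug stop.** A reader might infer that catheter discomfort or being off acid suppression biases the comparison. Both groups have the same transnasal probe, the same preceding EGJ inflations and the same drug stop. These add noise and are not clearly differential.
- **Prevalence.** The inclusion criteria select for a history of symptoms, not for symptoms during a short test. Testing follows a day of liquid diet, an overnight fast and two hours without even water, with antacids allowed. Nothing in the protocol supports 30% or 50% symptomatic at that moment. Only the direction of the imbalance is plausible from the group definitions.
- **The volume steps.** A symptom that first appears at 30 mL or above remains interpretable. The ambiguity centres on reports at 20 mL.
- **The cited method.** The EndoFLIP measurement follows an earlier published protocol that is not at hand. It is introduced for distensibility, and 5.2.2 writes out the symptom question without a baseline, so it does not clearly fill the gap.
- **Rank of the parameter.** It is not among the three main secondary parameters named in 4.4, and sensitivity is also tested with acid.

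These objections limit the size and reach of the problem. They do not supply the missing baseline.

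**Conclusion.** The point holds as a limited design weakness. As written, a symptom reported at 20 mL is ambiguous, and the ambiguity can favour a group difference because ongoing symptoms are more likely in the group chosen for having them.

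Its size is unknown. Under the stated assumptions there is almost no inflation at 10% v 5% (about 5–6%), some at 20% v 5% (about 7–12%), and more at 30% v 5% (about 12–30% over both analyses). The last range includes a 5% step response and the one before it does not, so 12% is not an upper bound for that case. A reader might take the 67% obtained at 50% v 5% as the expected error. It requires half the symptom group to be symptomatic before inflation, the 10% step response, and every such symptom counted; the documents support none of these.

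One lower-tier secondary parameter is affected. The primary parameter and the sample size are not.

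**What to change.** In 5.2.2, add a step: once the bag is 10 cm above the LES and still empty, ask the same question and record each symptom present. In the group comparison, count at each volume only a symptom that is new or worse than at 0 mL. To judge worsening, subjects can be asked whether a recorded symptom has changed, as the acid test already does each minute. In 5.1.2, write distension in place of distensibility so that the parameter matches the Summary and the Objectives.

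The cost is one extra question and one line in the case record per patient, with no added procedure. Some information is lost in patients already symptomatic at 0 mL, for whom a mild response to distension may be hard to recognise. The baseline removes most of the possible bias but not all: a symptom that worsens by itself during the series would still be counted.
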